### Plans to promote participant retention and complete follow-up {18b}

Participants will receive reminders for the different assessment points (post-treatment, 1-month, and 6-month follow-ups). These communications will focus solely on the data collection schedule, without providing additional details about the content of the intervention.

If participants discontinue the intervention but agree to remain in the study, follow-up data will still be collected to uphold the intention-to-treat analysis. The reasons for discontinuation and the nature of collected data will be documented to ensure transparency and accuracy in reporting.

### Data management {19}

Data entry, coding, security, and storage will adhere to strict protocols to ensure confidentiality and accuracy. Each participant will be assigned a unique three-digit key code (001–200), linked to personal information via a list accessible only to two designated researchers. This list will be destroyed at the study’s conclusion to safeguard privacy. Sensitive data will be stored on secure servers at Tilburg University, with anonymized datasets archived in Dataverse, the university’s centralized research data repository.

To ensure pseudonymization during data collection, participants will be assigned a unique code before completing questionnaires. Participants will only enter this code on their questionnaires, avoiding any personal identifiers. If researchers assist in completing the questionnaires, they will not record identifying details, linking responses solely to the assigned code. Digital surveys will be configured to prevent the collection of IP addresses or other metadata that could compromise pseudonymization. A separate logbook will securely store the key linking participant names to codes, which will be permanently deleted upon study completion. Researchers involved in data collection will receive training from the study coordinator to ensure compliance with these anonymization protocols. All pseudonymized data will be stored on secure servers at Tilburg University for a period of 15 years, in line with Dutch regulations, after which they will be destroyed.

A comprehensive logbook will document all data collection activities, including measurements, dates, and participant details. The data management plan will follow FAIR principles (Findable, Accessible, Interoperable, Reusable), ensuring future usability while adhering to international privacy regulations overseen by institutional privacy officers. Findings will be disseminated through open-access publications and relevant platforms.

### Confidentiality {27}

All research data will be securely stored in restricted-access facilities. Participant privacy will be upheld using unique key codes that are linked to personal information only via an encrypted list. Data will be pseudonymized to ensure separation from personal identifiers. Researchers assisting in questionnaire completion will follow strict pseudonymization procedures, ensuring that no names or direct identifiers are recorded with responses.

Data sharing with third parties will require a “Data Transfer Agreement” (DTA) approved by Tilburg University’s Ethics Review Board. Sensitive data will remain on secure university servers, with pseudonymized datasets archived for future research in compliance with FAIR principles. Study findings will be published in open-access journals and shared via organizational platforms..

### Plans for collection, laboratory evaluation, and storage of biological specimens for genetic or molecular analysis {33}

This study does not involve the collection or storage of biological specimens, as noted in the “ Additional consent provisions for collection and use of participant data and biological specimens {26b}” section).

## Statistical methods

### Statistical methods for primary and secondary outcomes {20a}

Data analysis will be conducted using R version 4.5.0 or later [41], following standard procedures for descriptive and inferential analyses.

The primary objective of this RCT is to assess the effectiveness of the Beat the Kick intervention compared to CAU in enhancing autonomous motivation for substance abuse treatment among adults with MID. It is hypothesized that participants in the Beat the Kick group will exhibit greater improvement in autonomous motivation from pre-test to post-test compared to the CAU group, with an anticipated medium effect size.

Linear mixed models (LMM) will be employed to test this primary hypothesis using the lme4 package in R [42]. LMMs are particularly suited for repeated measures data, accommodating both fixed and random effects [42]. Models will include fixed effects for group (Beat the Kick vs CAU), time (T1–T4), and the group × time interaction (primary effect of interest), with random intercepts and random slopes for time at the participant level to capture individual trajectories. The randomization stratification variable “addiction type” (alcohol vs cannabis/other drugs) will be included as a fixed effect in all models to adjust for baseline heterogeneity between strata; exploratory interaction terms with group and time (e.g., group × time × addiction type) will be examined to assess effect modification [43]. Baseline outcome values will serve as covariates to control for initial differences, mitigating regression to the mean [44].

Analyses will primarily adhere to the intention-to-treat (ITT) principle, preserving the integrity of randomization and providing a conservative estimate of the intervention’s effectiveness [45]. This approach ensures that all participants are analyzed in their originally assigned groups, irrespective of adherence or dropout. Complementary per-protocol (PP) analyses will also be conducted for participants who completed the intervention as intended, providing additional insights. Missing data will be handled using maximum likelihood estimation, a robust method that assumes data are missing at random, leveraging all available information without requiring imputation [46].

Potential confounders, such as living arrangements (e.g., 24-h supervised care, outpatient services, or home-based support) and prior substance use treatment exposure, will be incorporated as covariates. These factors are expected to influence engagement and outcomes by shaping daily routines, support systems, and environmental stability. Trainer effects, which may vary due to differences in style, experience, or engagement, will be modeled as a random effect to minimize potential bias. Additionally, to prevent carry-over effects, trainers will be exclusively assigned to the intervention group, ensuring that training specific to Beat the Kick does not unintentionally influence CAU.

The secondary objective is to evaluate the intervention’s effectiveness in reducing substance use among adults with MID. It is hypothesized that the experimental group will show a greater reduction in substance use levels compared to the CAU group at follow-up. LMMs for secondary outcomes will mirror the primary model, including addiction type as a fixed effect (with exploratory interactions), and will adjust for baseline substance use levels.

To accommodate the Zelen design’s pre-randomization process, analyses will carefully consider group allocation at the pre-randomization stage, ensuring that group comparisons accurately reflect the intervention’s true effect. Sensitivity analyses will assess the robustness of results, including tests with and without outliers. Missing data will be handled using full information maximum likelihood (FIML), a robust method that leverages all available data and is generally preferred regardless of the underlying missingness mechanism [47]. Although FIML does not eliminate all bias under not-missing-at-random (NMAR) conditions, it typically yields less biased results than listwise deletion. Conclusions drawn under NMAR will be interpreted with appropriate caution, and the plausibility of the missing at random (MAR) assumption will be evaluated in light of the observed data structure and auxiliary variables.

Descriptive statistics will summarize baseline characteristics and outcome variables, including autonomous motivation and substance use levels. The normality of continuous variables will be assessed using the Shapiro-Wilk test [48] and visual inspection of histograms and Q-Q plots. Rather than applying data transformations or switching to non-parametric tests that may reduce interpretability and statistical power, linear mixed models will be retained even when normality assumptions are violated. This decision is supported by recent simulation research demonstrating the robustness of linear models to non-normal data, particularly in the context of hypothesis testing [49]. To safeguard validity, diagnostic checks (e.g., Cook’s distance, leverage values) will be conducted to detect influential data points. Where necessary, sensitivity analyses will be performed with and without such points to assess their impact on the results.

To ensure reliability and validity, Cronbach’s alpha will assess the internal consistency of scales [50], while intraclass correlation coefficients (ICCs) will evaluate reliability across repeated measures [51]. The results section will detail the statistical techniques employed, including maximum likelihood estimation for incomplete data [52], and highlight how LMMs effectively capture fixed and random effects, providing insights into individual variability and longitudinal trends. This rigorous methodology supports robust and interpretable findings (Table 3).

**Table 3 Tab3:** Statistical analysis

	**Measure**	**Type of data**	**Timepoints**	**Statistical analysis**	**Subjects**
Motivation and psychological needs	TSRQ	Continuous	4	Linear Mixed Models	ITT, PP
	BPNSFS-ID	Continuous	4	Linear Mixed Models	ITT, PP
Substance use	SumID-Q	Continuous	4	Linear Mixed Models	ITT, PP

*ITT*, intention-to-treat analysis, including all randomized participants in the analysis; *PP*, per-protocol analysis, focusing on participants who adhered strictly to the protocol

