**Methods:**

Open-label, multicenter superiority randomized controlled trial in the Netherlands. We will recruit 138 adults (≥ 18 years) with MID or borderline intellectual functioning (intelligence quotient (IQ) 50–85 with adaptive limitations) and hazardous substance use (Alcohol Use Disorders Identification Test (AUDIT) ≤ 19 or Drug Use Disorders Identification Test (DUDIT) ≤ 24; ≥ 12 months) from six intellectual-disability care organizations. Recruitment will be conducted jointly by researchers from Tilburg University and care professionals at the participating organizations. In a Zelen pre-randomization design, eligible clients will be randomized 1:1 to Beat the Kick or CAU using a centralized computer-generated sequence with variable block sizes, stratified by addiction type (alcohol vs cannabis/other drugs). Tilburg researchers will obtain informed consent after allocation (intervention: consent for intervention + assessments; CAU: consent for assessments only). As an open-label trial, only the statistical analyst will remain blinded to allocation via A/B-coded datasets; the allocation key is held by an independent coordinator until primary analyses are complete. Assessments occur at T1 (pre), T2 (post), T3 (1 month), and T4 (6 months). Safety is monitored at T2–T4 through systematic adverse event (AE) and serious adverse event (SAE) recording, and serious events are reported to the Ethics Review Board within 24 h.Primary outcome: autonomous motivation (Treatment Self-Regulation Questionnaire; 15 items; 1–5 scale). Secondary outcomes: substance use ( Substance Use and Misuse in Intellectual Disability Questionnaire (SumID-Q) with AUDIT (0–40; ≥ 8 hazardous; ≥ 20 probable dependence) and DUDIT (0–44; ≥ 6 men/ ≥ 2 women hazardous; ≥ 25 probable dependence)), satisfaction and frustration of psychological needs (Basic Psychological Need Satisfaction and Frustration Scale – Intellectual Disability Version (BPNSFS-ID); 24 items; 1–5), treatment engagement (yes/no), and participant satisfaction. Primary analyses will use intention-to-treat linear mixed-effects models with fixed effects for group, time, and group × time, adjusting for the stratification variable.

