### Outcomes {12}

The primary outcome is the change in autonomous motivation for substance-abuse treatment, measured using an adapted version of the TSRQ [21]. The TSRQ comprises 15 items rated on a 5-point Likert scale (1 = completely untrue; 5 = completely true). Subscales are scored as means (range 1–5) and include autonomous motivation (internal consistency α≈0.84; primary endpoint), controlled motivation (α≈0.78), and amotivation (α≈0.41; analyzed exploratorily due to lower reliability). As participation in the intervention and any subsequent treatment is voluntary, baseline motivation may be relatively high; this will be considered when interpreting change. Assessments will occur at pre-treatment (T1), post-treatment (T2), and follow-ups at 1 month (T3) and 6 months (T4), with the primary endpoint defined as Δ(T2–T1) on autonomous motivation and maintenance examined at T3/T4. To optimize comprehension for MID/BIF participants, all self-reports will be interviewer-assisted.

Secondary outcomes include reductions in substance use and related problems, measured with the SumID-Q (patterns, frequency, consequences), which embeds the AUDIT and DUDIT screens. The AUDIT has 10 items (item scores 0–4; total 0–40) with commonly used cut-offs ≥ 8 for hazardous use and ≥ 20 for probable dependence. The DUDIT has 11 items (item scores 0–4; total 0–44) with cut-offs for hazardous use of ≥ 6 for men and ≥ 2 for women, and ≥ 25 for probable dependence. Both continuous totals and categorical classifications (none/hazardous/probable dependence) will be analyzed at T1, T2, T3, and T4 (recall periods per instrument guidance). Psychological need satisfaction and frustration will be assessed with the Basic Psychological Needs Satisfaction and Frustration Scale – Intellectual Disabilities (BPNSFS-ID; 24 items, 5-point Likert), yielding mean scores (range 1–5) for autonomy, competence, and relatedness (higher satisfaction = greater fulfillment; higher frustration = greater need thwarting) at T1, T2, T3, and T4 [35].

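### With T1–T4 as responses, addiction type, living arrangements and prior treatment as main effects give the T2–T1 group contrast almost no adjustment; {20a} must settle which model is meant

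*Protocol article*

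**What the plan says.** Outcomes {12} sets the target: "with the primary endpoint defined as Δ(T2–T1) on autonomous motivation and maintenance examined at T3/T4".

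Statistical methods {20a} gives the fixed part of the model: "Models will include fixed effects for group (Beat the Kick vs CAU), time (T1–T4), and the group × time interaction (primary effect of interest". Each participant also has a random intercept and a random time slope. Table 3 lists four timepoints for the TSRQ.

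On the covariates:
- Addiction type, the only stratification factor, "will be included as a fixed effect in all models to adjust for baseline heterogeneity between strata". On its interactions, the plan adds: "exploratory interaction terms with group and time (e.g., group × time × addiction type) will be examined to assess effect modification".
- Living arrangements and prior substance use treatment are named as potential confounders and enter as covariates, with no time interaction stated. The reason given is: "These factors are expected to influence engagement and outcomes by shaping daily routines, support systems, and environmental stability".
- The baseline outcome is also a covariate: "Baseline outcome values will serve as covariates to control for initial differences, mitigating regression to the mean".

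The Abstract summarises the primary analysis as "fixed effects for group, time, and group × time, adjusting for the stratification variable". The models for secondary outcomes are to mirror the primary one.

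**The concern.** The endpoint is a within-person change, and the three factors do not vary within a person. When T1 is one of the responses, a main effect of such a factor describes how high a participant's whole profile lies, not how far it moves from T1 to T2. The terms that would adjust the change are factor × visit interactions. For addiction type these fall among the exploratory terms; for the other two none is stated.

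Two things are at stake. First, randomisation is stratified by addiction type, but the primary test hardly uses that factor. If the strata change by different amounts, the difference stays in the residual and the SE is larger than it need be. Second, living arrangements and prior treatment are not stratified, so chance imbalance between arms is possible. Any effect they have on change would remain in the estimate, although the report would describe it as adjusted for them.

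**Working it through.** **1. The plan's own figures.** Sample size {14} uses f = 0.25, four measurements, ρ = 0.5, ε = 1, two-sided 5% and 80% power. For the between-group test, λ = f²·N·m / (1 + (m − 1)ρ) = 0.0625 × 82 × 4 / 2.5 = 8.2 on 1 and 80 df, which gives power 0.808. Dropout of 40% gives 82 / 0.6 = 136.7, so 137, or 138 for equal arms. Both 82 and 138 reproduce, and this point changes neither.

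**2. Algebra.** Let ȳ_gt be the mean in arm g at visit t, x̄_g the covariate means in arm g, and β the common covariate slopes. With complete data and a free mean for every arm and visit, the adjusted mean is ȳ_gt − x̄_g′β. The T2–T1 change within arm g is (ȳ_g2 − x̄_g′β) − (ȳ_g1 − x̄_g′β) = ȳ_g2 − ȳ_g1. β has gone, whatever its estimate and whatever the covariance, so the group difference in change is the same with or without the covariates.

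**3. Simulation.** N = 138, 1:1 allocation stratified by addiction type, random-intercept or random-slope covariance, true effect 0.5, outcome SD about 1. Covariate effects and variances are assumptions, because the protocol gives none. Entries are absolute shifts in the T2–T1 group contrast relative to the model without covariates, in SD units.

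| Data | Main effects: mean (largest) | Covariate × time: mean (largest) |
|---|---|---|
| Complete, 600 trials | 0 (5e-15) | 0.014–0.016 (0.11) |
| 40% dropout at random given observed data, maximum likelihood | 0.009–0.012 (0.044) | 0.016–0.024 (0.12) |

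In the complete-data random-intercept setting, the SE with variances treated as known was 0.1703 both without covariates and with main effects.

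**4. One simulated dataset, fitted by mixed model (random intercept, REML).**

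| Data | No covariates | Main effects | Covariate × time |
|---|---|---|---|
| Complete | 0.58118 (SE 0.16846) | 0.58118 (SE 0.16846) | 0.55574 (SE 0.16489) |
| 40% dropout | 0.616 (SE 0.181) | 0.596 (SE 0.180) | 0.554 (SE 0.176) |

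Adding a random slope leaves the complete-data estimates unchanged. The first two SEs then differ only because the variance components are re-estimated (0.1674 and 0.1682).

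**5. The other reading.** With T2–T4 as responses and T1 as covariate, adding the three factors as main effects moves the T2 contrast from 0.526 (SE 0.163) to 0.486 (SE 0.148). Main effects do adjust there.

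**6. Size of the loss.** If the factors explain a share R² of the variance in change, leaving them out multiplies the SE by 1/√(1 − R²): 1.026 at R² = 0.05, 1.054 at 0.10 and 1.118 at 0.20. In variance terms this equals losing 5–20% of participants. The range of R² is assumed.

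**7. Price of the extra terms.** Where no factor affected change (complete data, random intercept), the known-variance SE rose from 0.1703 to 0.1715 with covariate × time terms. The ratio is 0.1715 / 0.1703 = 1.007, or under 1%.

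**The case against.** The strongest reply is that {20a} is ambiguous rather than wrong. Baseline as a covariate is the usual mark of a model for post-baseline visits, and step 5 shows that main effects adjust in that model. This stands as far as it goes. But that reading does not fit time running from T1 to T4 or the four timepoints in Table 3, so the section has to say which model it means.

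A second reply is that the text speaks of baseline heterogeneity between strata. A main effect does describe that level difference, and differencing removes it anyway. This also stands: the plan does not expressly promise to adjust the change. It follows that stable level differences cannot bias the contrast. A reader might infer a biased or invalid primary test, and the documents do not support that.

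Third, a condensed article may leave factor × visit terms to the analysis plan. This has some force for living arrangements and prior treatment, where main effects only is inferred from their being called covariates. It has less for addiction type, whose interactions the article itself places outside the confirmatory model.

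Two further inferences would go too far:
- **That the factors drop out altogether.** This is exact only for complete data. Under the expected dropout of about 40% and maximum likelihood they do enter, though weakly and as a by-product of missingness.
- **That the problem would persist if both arms were constrained to a common T1 mean.** The T2 effect is then Δ2 − bΔ1, where Δt is the arm difference at visit t and b < 1. A covariate imbalance d contributes (1 − b)βd, so main effects partly adjust. In simulation (N = 82, complete data, assumed covariate effects of 0.3 to 0.5 SD) they moved the estimate by 0.042, 0.027 and 0.017 SD on average at correlations 0.3, 0.5 and 0.7.

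**Conclusion.** The point holds for the model as literally written: T1–T4 as responses, free arm means and group × time as the primary effect. With complete data, the T2–T1 contrast gets no adjustment from addiction type, living arrangements or prior treatment. With the expected dropout the adjustment is about 0.01 SD on average and incidental.

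The consequence is lost precision and uncorrected chance imbalance in whatever affects change. No bias, type I error inflation or change in sample size is shown. The 3–12% excess in the SE depends wholly on the assumed 5–20% of variance explained. The protocol expects living arrangements and prior treatment to influence outcomes, but does not say whether they act on level or on change; only the latter matters here. A correction is worth making because it is cheap and because {20a} must in any case settle whether T1 is a response or a covariate.

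**What to change.** Amend {20a} in one of two ways:

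- **T2–T4 as responses:** T1 as a covariate, with addiction type, living arrangement and prior treatment as main effects.
- **T1–T4 as responses:** addiction type × visit, living arrangement × visit and prior treatment × visit as part of the confirmatory model.

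In both, leave only the effect-modification terms exploratory (covariate × group and covariate × group × time). Align the Abstract and the secondary models, which follow the primary one.

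The change is to analysis wording only and uses variables already to be collected. It costs a few degrees of freedom; in the check above, less than 1% on the SE when the factors have no effect on change.

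### The primary mixed model uses T1 as both response and covariate, so the covariate does not adjust the T2–T1 effect, and the effect named as primary is the whole group × time interaction instead of the T2–T1 contrast

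*Protocol article*

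**What the plan says.** The Outcomes section ({12}) sets the endpoint, "with the primary endpoint defined as Δ(T2–T1) on autonomous motivation and maintenance examined at T3/T4". The hypothesis in {20a} agrees with it: "greater improvement in autonomous motivation from pre-test to post-test compared to the CAU group".

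The model given in {20a} to test that hypothesis has "fixed effects for group (Beat the Kick vs CAU), time (T1–T4), and the group × time interaction (primary effect of interest"), together "with random intercepts and random slopes for time at the participant level to capture individual trajectories". Table 3 lists four timepoints for the TSRQ, so T1 is one of the modelled responses. The same paragraph then enters the T1 score a second time: "Baseline outcome values will serve as covariates to control for initial differences, mitigating regression to the mean".

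The protocol does not say whether time is categorical or linear, and it names no contrast at T2. The structure carries over to other outcomes: "LMMs for secondary outcomes will mirror the primary model", with adjustment for baseline substance use. Table 3 lists linear mixed models over four timepoints for the BPNSFS-ID and SumID-Q as well.

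**The concern.** Two separate faults lie in what the protocol states.

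**The covariate does not do its stated job.** A participant's T1 score is constant over that participant's visits. If it enters with one slope, it adds the same amount to the fitted T1 and T2 values and drops out of their difference. It can explain differences in level between participants but not differences in change. The promised control of initial differences and regression to the mean therefore does not reach the primary effect. Readers would expect that control here, because eligibility requires low autonomous motivation on the same TSRQ.

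**The named effect is not the endpoint.** The endpoint is one difference, at T2. The group × time interaction over T1–T4 also covers T3 and T4, which the protocol reserves for maintenance. A significant interaction need not involve T2, and a real effect at T2 can be diluted by the other visits.

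The stakes are a less precise primary comparison than the data allow, and a headline test that may answer a different question from the one registered as primary.

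**Working it through.** **Inputs.** From Sample size {14}: f = 0.25, two-sided 5%, 80% power, correlation r = 0.5 (a software default), sphericity, 82 evaluable participants (41 per arm), about 40% dropout and a target of 138. From Trial design {8}: 69 per arm. For two groups d = 2f = 0.5. No SD is given, so effects are in SD units. The calculations ignore trainer clustering and the other covariates.

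**The plan's own figure.** For a group main effect averaged over four visits, λ = f²·N·m/(1 + (m − 1)r) = 0.0625 × 82 × 4/2.5 = 8.2. With 1 and 80 df the power is 0.808, so 82 is reproduced. The G*Power formula for a group × time interaction would give 24 (four visits) or 34 (two visits). Allowing for dropout, 82/0.6 = 136.7, consistent with 138.

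**1. Cancellation.** Let γ be the slope of the baseline covariate. Its contribution to the T2–T1 difference is γY₁ − γY₁ = 0. With complete data the group × T2 coefficient is therefore the raw between-arm difference in mean change, with or without the covariate. Simulated fits (r = 0.5) with the covariate and participant random slopes confirm this:

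| Complete data set | Without T1 covariate | With T1 covariate | T2 adjusted for T1 (ANCOVA) |
|---|---|---|---|
| 1 | 0.3196 | 0.3196 | 0.3902 |
| 2 | 0.4698 | 0.4698 | 0.4409 |
| 3 | 0.4430 | 0.4430 | 0.5299 |

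With about 40% or more dropout, the covariate moves the estimate a little but does not turn it into the adjusted one:

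| Data set with dropout | Without | With | ANCOVA |
|---|---|---|---|
| 1 | 0.643 | 0.620 | 0.599 |
| 2 | 0.342 | 0.360 | 0.318 |
| 3 | 0.237 | 0.227 | 0.135 |

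**2. Cost in precision.** In units of the outcome SD, the SD of a change score is √(2(1 − r)) and the SD of T2 adjusted for T1 is √(1 − r²). At r = 0.5 these are 1.00 and 0.866, so the variances are 1.00 and 0.75. Power comes from the noncentral t with noncentrality (0.5/SD)·√(n/2). At n = 41 and r = 0.5 that is 0.5 × √20.5 = 2.26 for the change score and 2.26/0.866 = 2.61 for the adjusted comparison.

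| n per arm at T2 | r | Change score (as specified) | Adjusted for T1 |
|---|---|---|---|
| 41 | 0.3 | 0.47 | 0.65 |
| 41 | 0.5 | 0.61 | 0.73 |
| 41 | 0.7 | 0.82 | 0.88 |
| 55 | 0.5 | 0.74 | 0.85 |
| 69 | 0.5 | 0.83 | 0.92 |

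**3. The named interaction, with categorical time.** For between-arm differences e at the four visits, λ = (n/2)·Σ(e − ē)²/(1 − r), on 3 and 3(2n − 2) = 240 df at n = 41.

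- Effect at T4 only, e = (0, 0, 0, 0.5): ē = 0.125 and Σ(e − ē)² = 0.1875, so λ = 20.5 × 0.1875/0.5 = 7.69 and power is 0.63.
- Effect at T2 only, e = (0, 0.5, 0, 0): the same λ, so again 0.63. The test does not distinguish the two cases.
- Effect at T2 that fades, e = (0, 0.5, 0.25, 0.125): λ = 5.61 and power is 0.48, against 0.61 for the single T2–T1 contrast and 0.73 for the adjusted one.

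**4. Points that depend on how time is coded.** If time were linear in weeks (0, 10, 14.3, 36), a step δ held to T4 would imply a T2–T1 effect of 0.22δ, and an effect fading as δ, 0.5δ, 0 would imply −0.08δ. If instead time were categorical in the random part too, each person would have four random effects for at most four observations (4 × 138 = 552 for 552), and the residual variance would not be separately identifiable. Both cannot apply to one coding of time, and the protocol states neither.

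**The case against.** The strongest defence is that nothing here biases the T2 result. Under randomisation, regression to the mean acts on both arms alike in expectation, and the group × T2 coefficient is exactly the change-score difference that the Outcomes section defines. That stands: a reader might infer a biased primary estimate, and the documents do not support it. The loss is one of precision and of the adjustment promised.

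It can also be said that with categorical time the T2 contrast is one coefficient of the interaction, and that naming the contrast and the coding is detail left to an analysis plan that is not shown. The first part is true. The second answers only what is missing. The article itself fixes T1–T4 as responses, T1 as covariate and the whole interaction as the effect of interest, so a plan that follows it inherits the fault. Dropping T1 from the responses alone would not help, because group × time over T2–T4 would no longer be the treatment effect.

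A reader might also infer that the primary effect can take the wrong sign, or that the random-effects model cannot be fitted. The text supports neither. The sign reversal needs linear fixed time and an assumed fading effect. The identifiability failure needs categorical random slopes, whereas one linear slope per person alongside categorical fixed time is a possible reading and can be fitted.

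Finally, 0.61 against 0.73 is one point in a range. It rests on a default r and on all dropout falling before T2, which the protocol does not say. The gap narrows with higher r or better retention at T2.

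**Conclusion.** Both faults hold, within limits. As specified, the T1 covariate leaves the T2–T1 contrast unadjusted: exactly so with complete data, and nearly so in the simulated fits with dropout. The contrast remains unbiased but less precise than it should be. At d = 0.5, the loss in power is 6 to 18 percentage points at 41 per arm for r between 0.7 and 0.3, and 9 points (0.83 against 0.92) at r = 0.5 with all 69 per arm observed at T2.

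The more consequential fault is the named test. With categorical time, the group × time interaction is as likely to be significant for an effect at T4 alone as for an effect at T2 alone (about 0.63 each at 41 per arm, r = 0.5), so it can support a conclusion that the primary endpoint does not. The visit profiles used to show this are assumptions. The statements about linear time and about 552 random effects are conditional on a coding that the protocol does not give, and the conclusion does not rest on them.

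**What to change.** Choose one structure and state it before the analysis:

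- (a) T2–T4 as responses, with T1 and T1 × time as covariates; or
- (b) T1–T4 as responses, with the T1 mean constrained to be common to both arms and no T1 covariate.

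In either case:

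- Use categorical fixed time and name the 1-df group difference at T2 as the single primary test, with T3 and T4 as maintenance.
- Keep addiction type as a fixed effect and the planned trainer random effect.
- Specify a within-person covariance that is identifiable with four visits. If time is categorical, do not fit random slopes for every visit plus a residual. Name software that can fit the chosen structure; the protocol currently names only lme4.
- Apply the same baseline structure to the BPNSFS-ID and substance-use models.

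The cost is revised wording in {20a} and in the analysis plan, and a different model call, possibly in different software. No new data are needed.
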